| Study Design           | Prospective, Randomized, Multicenter, open-label, phase III trial                                                                                                                                                                                                                                                                                                                                                                                                                                                                                                                                                                                                                                                                                                                                                                                                                                                                                                                                                                                                                                                                                                                                                                                                                                                                                                                                                                    |

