iii. Radiotherapy plan: 3D-CRT or IMRT technology is used; PTV is externally applied in the anterior-posterior and left-right directions by 0.8 cm on the basis of CTV, and externally applied in the up-and-down direction by 1.0 cm; 95% of the PTV has a minimum dose of 50.4 Gy/28f; hotspot dose is  $\leq 107\%$  of the prescribed dose, and the volume is  $\leq 2$  CC; the target area conformity is  $\geq 0.8$ ; spinal cord is  $\leq 40$  Gy, and the liver V30 is  $\leq 33\%$  of the dose. The maximum dose received by 33% of the volume of one kidney (mostly right kidney) is  $<15$  Gy, and the average of both kidneys is  $<15$  Gy; D50 of small intestine is  $<20-30$  Gy.

4.5 Effectiveness evaluation: patients should undergo effectiveness evaluation at least once every 6 months during the first year after enrolment; after the end of treatment, regular follow-up and effectiveness evaluation should be conducted in accordance with the requirements of the supervising physician, and effectiveness evaluation should be conducted

at least once every 6-12 months. The time intervals of the evaluation should all be referenced to the point in time when the patient was randomised to the group. The evaluation includes physical examination, imaging (CT, chest radiograph, ultrasound, etc.) and laboratory tests (routine blood, blood biochemistry, tumour markers, etc.). The primary study endpoint was 3-year DFS, which was defined as the time from randomisation to the occurrence of tumour recurrence/metastasis (i.e., disease progression), or death in the randomised group; the secondary study endpoint of 3-year OS referred to the time from randomisation to death; and safety was also included.

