## 10.4 Statistical methods

All clinical data were analyzed using IBM SPSS Statistics (IBM Corp., Armonk, NY, USA. version 29.0) and R software (version 4.2.1). Categorical variables were compared with the use of Chi-squared test or Fisher's exact test. Kaplan–Meier method was used to analyses the DFS and OS, log-rank test to assess the significance, and Cox

proportional hazards model to calculate hazard ratio (HR). The median follow-up time was calculated by reverse-KM method. Statistical significance was defined as a two-side P value < 0.05.

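### After treatment, the interval between recurrence evaluations is left to the supervising physician in an open-label trial, so equal ascertainment of DFS in the two arms is not secured

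*Protocol*

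**What the plan says.** Section 4.5 of the protocol sets the evaluation schedule in two stages. In year 1, "patients should undergo effectiveness evaluation at least once every 6 months during the first year after enrolment". After treatment ends, "regular follow-up and effectiveness evaluation should be conducted in accordance with the requirements of the supervising physician", and this must happen "at least once every 6-12 months". The intervals have a common origin: "The time intervals of the evaluation should all be referenced to the point in time when the patient was randomised to the group". Each evaluation comprises physical examination, laboratory tests and imaging, the last as an open list: "imaging (CT, chest radiograph, ultrasound, etc".

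The same section defines the primary endpoint, DFS, as "time from randomisation to the occurrence of tumour recurrence/metastasis (i.e., disease progression), or death in the randomised group". The synopsis describes the design as "Prospective, Randomized, Multicenter, open-label, phase III trial". Section 10.4 names the analysis: Kaplan–Meier curves, a Cox hazard ratio, and a "log-rank test to assess the significance". The protocol nowhere requires the post-treatment frequency to be the same in the two arms.

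**The concern.** A recurrence without symptoms enters the data on the day someone looks for it. An arm evaluated yearly will therefore appear to recur later than an arm evaluated half-yearly, even if the disease behaves identically. Here the interval is set by a physician who, in an open-label trial, can be expected to know the arm, and the stated minimum spans a factor of two. It is also only a minimum, so shorter intervals are permitted too. The open imaging list adds a second route by which detection could differ.

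The log-rank test and Cox model take event dates as given and do not correct for unequal detection times. At stake is the primary comparison: unequal evaluation could create an apparent DFS difference or hide a real one. A later analysis plan cannot recover scans that were never done, so this belongs in the protocol.

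**Working it through.** The plan gives no figure on this point to reproduce, so the check asks how far the permitted range could move the planned comparison.

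**Inputs from the protocol.** 3-year DFS 70% versus 78%, two-sided 0.05, 516 evaluable and 620 enrolled (section 10.3); 1:1 allocation (section 4.1); schedule from section 4.5; log-rank test (section 10.4).

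**Assumptions.** Exponential DFS; 10% or 15% of first events are deaths, dated exactly; all recurrences found at the next visit; visits at 6 and 12 months, then every 6 or 12 months; patients without a recorded event counted as event-free up to the cut-off. Late visits carry a half-normal delay with sigma 0.06 years.

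**Step 1: parameters.** Hazard = −ln(0.70)/3 = 0.119 per year. Planned HR = ln(0.78)/ln(0.70) = 0.697.

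**Step 2: the gap in the curves, by hand.** With a share f of first events being deaths, and u the last completed visit before t, apparent DFS(t) = f·S(t) + (1 − f)·S(u). Take true 3-year DFS of 70% in both arms and read the curves just before the 3-year visits.
- 6-monthly arm, u = 2.5: S = 0.70^(2.5/3) = 74.3%.
- 12-monthly arm, u = 2.0: S = 0.70^(2/3) = 78.8%.
- Gap = (1 − f) × 4.5 points: 4.5 with no deaths, and 0.85 × 4.5 = 3.8 with f = 0.15.
- Once the 3-year visits are done, u = 3 in both arms and the gap is 0.

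**Step 3: false positives with no true difference.** Simulated one-sided rate favouring the less-scanned arm (nominal 2.5%). Ranges are over separate sets of runs.

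| Scenario | Rate |
|---|---|
| Equal intervals | about 2.5–3% |
| All 12- vs all 6-monthly, follow-up staggered 3–6 years | 6.4–7.5% |
| Same split, cut-off exactly 5.0 years, late visits | 10.3–12.0% |
| Same split, cut-off 4.75 years, late visits | 11.0% |
| Same split, cut-off 5.0, on-time visits, 5-year visit counted | 3.9–4.7% |
| Same split, cut-off 5.25 years, late visits | 3.7–3.8% |
| 60% vs 40% seen yearly, cut-off 5.0 / 5.25 | 4.1% / 2.5% |

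With 516 patients, staggered follow-up and 10% deaths (1,500 runs; Monte Carlo error about 0.6 points on these rates), the apparent HR is 0.935 when the chemoradiotherapy arm is seen yearly. It is 1.076 when the SOX arm is, with 6.5% false positives then favouring SOX.

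**Step 4: a true HR of 0.697, same settings.**

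| Schedule after year 1 | Apparent HR | Power |
|---|---|---|
| Both 6-monthly | 0.69 | 67% |
| Both 12-monthly | 0.69 | 66% |
| Chemoradiotherapy 12, SOX 6 | 0.648 | 80% |
| Chemoradiotherapy 6, SOX 12 | 0.740 | 50% |

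The Monte Carlo error on power is about 1.2 points. With a 6- versus 9-month split, power is 74% or 59%, depending on which arm is seen less often. The 67% baseline lies below the planned 80%; that is a separate sample-size matter on which this point does not depend.

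**Step 5: everyone censored at exactly 3 years with visits on the grid.** The null HR is 0.974 or 1.031, so the distortion is small.

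**The case against.** The case against has four parts.

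First, nothing in the protocol ties interval to arm. The rule is the same for both, and randomisation should balance patient-level reasons for closer follow-up. The all-yearly versus all-half-yearly split is an extreme; at 60% versus 40% the effect is nearly gone. This stands, and it limits the size claimed.

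Second, the larger figures depend on where the cut-off falls. A reader might infer from the 10–12% rates that the type I error is inflated four- to fivefold. The documents do not support that: the protocol names no 5-year cut-off, and those rates arise when the cut-off falls after the half-yearly arm's last visit but before the yearly arm has completed its next one. Moving the cut-off to 5.25 years brings the rate below 4%. Censoring event-free patients at their last evaluation would shrink the effect too, as would recurrences surfacing between visits: if 40% did so (an assumption), the worst case at a 5.0-year cut-off falls to 6.5%.

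Third, anchoring at randomisation does help. Both a 6-month and a 12-month grid have a visit at year 3, so the named 3-year endpoint is largely protected if visits are on time. This also stands. It does not cover a log-rank test over the whole curve, late visits, or patients on intermediate intervals.

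Fourth, OS is not affected by scan timing. True, but OS is secondary.

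These points reduce the magnitude. They do not supply the missing requirement of equal frequency.

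**Conclusion.** The concern holds as a risk that the protocol leaves open. Section 4.5 permits unequal post-treatment evaluation between arms in an open-label trial with a recurrence-based primary endpoint, and neither the randomisation anchor nor the year-1 minimum prevents this after year 1.

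The size is modest and conditional. For a full 12- versus 6-month split under staggered follow-up, the HR shifts by about 7% and the one-sided error is about 6–7% instead of 2.5%; across cut-offs and visit punctuality it runs from about 4% to 12%. A moderate imbalance gives about 3%. The 4-point gap at 3 years is a matter of reading the curve too early. All of this rests on the stated assumptions, above all the split itself, which is illustrative.

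A reader might also infer that follow-up will differ by arm, or that any bias favours chemoradiotherapy. The protocol supports neither: it shows no difference in practice, and the direction is unknown. Nor do the figures single out 6 months as the necessary interval, since equal 6-month and equal 12-month schedules perform alike. The protection comes from equality. A change is worth making because it is cheap and concerns the primary endpoint.

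**What to change.** In section 4.5, replace the discretionary range with one evaluation interval counted from randomisation, identical in both arms, chosen within the 6–12 months already allowed and kept at least through year 3. Name the imaging set for each scheduled visit and make it the same in both arms. State that scans requested by the physician are additional and do not replace or shift scheduled visits. State also that 3-year DFS is read only after the 3-year visits are complete.

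The cost is protocol wording and, if the shorter interval is chosen, some additional imaging visits for patients who would otherwise have been seen yearly.

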| Objectives             | Primary Endpoint: Disease-Free Survival (DFS).
Secondary Endpoint: Overall Survival (OS) and treatment-related adverse event.                                                                                                                                                                                                                                                                                                                                                                                                                                                                                                                                                                                                                                                                                                                                                                                                                                                                                                                                                                                                                                                                                                                                                                                                                                                                                                     |

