## 3 Objectives

The patients after D2 radical surgery for gastric cancer that meet the enrolment criteria were randomly assigned to be given SOX regimen combined with simultaneous radiotherapy or chemotherapy with SOX regimen alone, to explore the value of simultaneous radiotherapy after D2 radical surgery for gastric cancer.

- (1) The primary objective was: disease free survival (DFS).
- (2) The secondary objectives were: overall survival (OS), and various types of adverse events.

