# 10 Study assessment

10.1 Effective evaluation indicators: The primary purpose is: DFS. The secondary purpose is: and OS.

10.2 Safety evaluation index: including all toxic side effects and adverse events observed during the trial.

10.3 Sample content estimation: we hypothesised that synchronous radiotherapy would result in higher DFS. with a double significance level of 0.05 and a certainty of 80%. We expect that the 3-year DFS of SOX regimen combined with simultaneous radiotherapy can be at least 8% higher than that of the chemotherapy-only group, i.e., from 70% to 78%. Based on the sample size formula for the comparison of the two sample rates, the sample size needed for this project was calculated to be 516 patients; assuming that 20% of the patients would need to be excluded from the statistics, the total number of patients that would need to be enrolled in this project would be 620.

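### The primary endpoint is labelled 3-year DFS but defined and tested as time to event, and the stated 80% power is not delivered at 3 years, because 516 does not follow from its own inputs

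*Protocol*

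**What the plan says.** - **Endpoint.** Section 4.5 reads "The primary study endpoint was 3-year DFS, which was defined as the time from randomisation to the occurrence of tumour recurrence/metastasis" or death. The synopsis has "Primary Endpoint: Disease-Free Survival (DFS") and section 3 has "The primary objective was: disease free survival (DFS"), both without the 3-year label; section 10.1 also says only DFS.
- **Sizing.** Section 10.3 sets its error rates "with a double significance level of 0.05 and a certainty of 80" per cent. It expects 3-year DFS to rise, "i.e., from 70% to 78" per cent, with the number obtained "Based on the sample size formula for the comparison of the two sample rates". The result is that "the sample size needed for this project was calculated to be 516 patients", raised to 620 on the assumption that 20% will be left out of the analysis.
- **Test.** The synopsis and section 10.4 use Kaplan-Meier curves, "log-rank test to assess the significance", and a Cox model for the hazard ratio. No comparison of rates at 3 years is planned.
- **Timing.** The protocol gives intervals between assessments. It states no accrual period, minimum follow-up, number of events or truncation of the test at 3 years.

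**The concern.** A 3-year rate and a time to event are different quantities. One is summarised by a difference at a single time, the other by a hazard ratio over the follow-up used. Section 4.5 gives the label of the first and the definition of the second, section 10.3 sizes the first, and section 10.4 tests the second. The power of a log-rank test depends on the number of DFS events, yet the only horizon in the protocol is 3 years and no number of events is attached to it.

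At stake is whether the trial can detect the effect it was built for. If power at the primary analysis is well below 80%, a true gain of 8 percentage points may be reported as no difference.

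**Working it through.** **Inputs from section 10.3:** 3-year DFS 0.70 (control) and 0.78 (experimental), two-sided 0.05 (z = 1.960), power 80% (z = 0.8416), 516 evaluable, 620 enrolled. Allocation is 1:1 (section 4.1).

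**1. The plan's own figure.** Two-rate formula with pooled variance under the null, mean rate 0.74:

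n per arm = [1.960 × √(2 × 0.74 × 0.26) + 0.8416 × √(0.70 × 0.30 + 0.78 × 0.22)]² / 0.08² = 470.7, so 471 per arm and **942 in total**.

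Other two-sided versions give 936 (unpooled), 940 (arcsine) and 992 (continuity-corrected). One-sided versions give 738 to 792. None comes near 516. The step to 620 is 516 × 1.2 = 619.2; dividing by 0.8 would give 645.

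The two-rate test at 3 years has power of about 54% with 516 patients and 62% with 620.

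**2. Events the log-rank test needs.** Under proportional hazards, HR = ln(0.78)/ln(0.70) = 0.697 and ln(HR) = −0.3615.

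Events = 4 × (1.960 + 0.8416)² / 0.3615² = **240.2** (Schoenfeld; 241 rounded up). Freedman's formula gives 246.

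**3. Events if each patient contributes exactly 3 years.** The average event probability is (0.30 + 0.22)/2 = 0.26. Power = Φ(√D/2 × 0.3615 − 1.960), with D the number of events.

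| Patients analysed | Events | Log-rank power |
|---|---|---|
| 516 | 134 | 55% |
| 620 | 161 | 63% |
| 942 | 245 | just over 80% (245 exceeds 241) |

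The last row shows that the two-rate formula and the log-rank test call for nearly the same trial when the formula is evaluated correctly.

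**4. Events if all follow-up counts and the cut is 3 years after the last patient.** Assumptions not in the protocol: exponential hazards of −ln(0.70)/3 = 0.1189 and −ln(0.78)/3 = 0.0828 per year, uniform accrual over A years, no loss. The event probability per arm is 1 − [exp(−3λ) − exp(−(A+3)λ)]/(λA).

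| Assumed accrual | 620: events (power) | 516: events (power) |
|---|---|---|
| 2 years | 204 (73%) | 170 (65%) |
| 3 years | 223 (77%) | 186 (69%) |
| 4 years | 241 (80%) | 201 (73%) |

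**5. Time from the last patient to 240 events, same assumptions.** For accrual of 2, 3 and 4 years: 3.9, 3.4 and 3.0 years with 620 analysed; 5.3, 4.8 and 4.3 years with 516.

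**The case against.** Four arguments run the other way.

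- **The endpoint is clear enough.** The synopsis and sections 3 and 10.1 say DFS, the definition in 4.5 is a time to event, and the log-rank is the only significance test for it. This largely stands. The 3-year label is one stray term and is easily removed. It does not remove the power problem, because section 10.3 fixes its effect at 3 years.
- **The 3-year event counts are a floor.** This stands. Nothing truncates the log-rank test at 3 years, and patients enrolled early add events. A reader might infer that power is 55% to 63% whatever happens. The protocol does not support that, since it does not fix the cut, and with 620 analysed and 4 years of accrual the shortfall disappears.
- **A two-rate formula followed by a log-rank test is common and harmless.** This also stands here. A reader might infer that the mismatch of method and test is what loses the power. Steps 1 and 3 show otherwise: 942 patients would give about 245 events at 3 years. The loss comes from 516.
- **Data cut and event trigger usually belong in the SAP, which is not shown.** Fair, so their absence alone is not the point. Nor do the documents show that anyone intends to choose the cut after seeing data in this open-label trial. What remains is that the protocol claims 80% power for a number of patients that does not give it at the horizon it names.

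**Conclusion.** The concern holds in this form. The label and the definition in section 4.5 disagree, and the 80% power claimed in section 10.3 is not reached at 3 years under either reading: 54% to 62% for a comparison of rates and 55% to 63% for the log-rank test, for 516 to 620 patients. With the cut 3 years after the last patient and all follow-up counted, log-rank power is 65% to 73% with 516 analysed and 73% to 80% with 620.

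The cause is that 516 is about 45% below the 942 that its own inputs require (1 − 516/942 = 0.45). The two-rate figures rest only on the protocol's inputs. The event and log-rank figures add proportional hazards. The ranges by accrual add constant hazards, uniform accrual of 2 to 4 years and no loss to follow-up, none of which the protocol states.

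**What to change.** - **Section 4.5:** drop the 3-year label from the primary endpoint. Name time-to-event DFS, tested by log-rank, in line with the synopsis and sections 3 and 10.1. Report 3-year DFS as a descriptive Kaplan-Meier estimate.
- **Section 10.3:** replace the derivation of 516 with the hazard ratio and about 240 DFS events, and trigger the primary analysis at the 240th event. Give the ratio as 0.697 or say that 0.70 is rounded; taken literally, 0.70 would need 4 × 2.8016²/ln(0.70)² = 247 events.
- **Section 10.3:** analyse all 620 randomised patients and remove the assumption that 20% are left out.
- **If an event-driven analysis is not acceptable:** keep the 3-year horizon and state the power actually achieved, about 55% to 63%.

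**Cost.** Wording and time, with no extra patients. With all 620 analysed, 240 events arrive about 3.0 to 3.9 years after the last patient (accrual of 4 down to 2 years, assumed), so up to about one year beyond a 3-year cut. If only 516 are analysed, the wait is 4.3 to 5.3 years, or 1.3 to 2.3 years beyond that cut. Loss to follow-up would lengthen either.

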## **5 Selection of Patients**

### **5.1 Inclusion Criteria**

- (1) Age 18-70 years;
- (2) Gastric cancer patients who have been diagnosed by pathology and have been surgically resected;
- (3) Surgery is radical, achieving R0 resection, and D2 lymph node dissection (with organ preservation) (the number of lymph node dissection should be  $\geq 15$ );
- (4) The time to surgery is not more than 3 months;
- (5) According to the 2010 edition of UICC/AJCC staging criteria, postoperative pathological stage T stage  $\geq$  T4a, N stage  $\geq$  N0; and no tumour metastasis or postoperative recurrence is detected by comprehensive examination, i.e., the M stage is M0;
- (6) ECOG PS score: 0-1;
- (7) Patients who have not received radiotherapy and systemic chemotherapy before or after surgery;
- (8) Normal function of major organs, i.e., the following indications are met:
  - i. routine blood tests need to meet the following criteria: HB  $\geq$  9g/dL, WBC  $\geq$  3.5/4.0 $\times$  10^9/L, PLT  $\geq$  100 $\times$  10^9/L
  - ii. Biochemical tests must meet the following criteria: Crea and BIL  $\leq$  1.0 times the upper limit of normal (ULN), ALT and AST  $\leq$  2.5 times the upper limit of normal (ULN).
- (9) Women of childbearing potential must have had a negative pregnancy test (serum or urine) 7 days prior to enrolment and be willing to use an appropriate method of contraception for the duration of the trial and for 8 weeks after the last dose. For males, surgical sterilisation should be applied or agreement to use an appropriate method of contraception for the duration of the trial or 8 weeks after the final dose.
- (10) Subjects voluntarily enrolled in the study, signed an informed consent form, were compliant, and cooperated with follow-up.

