| Inclusion Criteria     | 
(1) Age 18-70 years;
 
(2) Pathologically confirmed gastric cancer patients who have undergone surgical resection;
 
(3) Surgery is radical, achieving R0 resection, and D2 lymph node dissection (with organ preservation) (the number of lymph node dissection should be <math>\geq 15</math>);
 
(4) The time to surgery is not more than 3 months;
 
(5) According to the 2010 edition of UICC/AJCC staging criteria, postoperative pathological stage T stage <math>\geq</math> T4a, N stage <math>\geq</math> N0; and no tumour metastasis or postoperative recurrence is detected by comprehensive examination, i.e., the M stage is M0;
 
(6) Eastern Cooperative Oncology Group (ECOG) performance score: 0-1;
 
(7) Patients who have not received radiotherapy and systemic chemotherapy before or after surgery;
 
(8) Normal function of major organs.
 
(9) Women of childbearing potential must have had a negative pregnancy test (serum or urine) 7 days prior to enrolment and be willing to use an appropriate method of contraception for the duration of the trial and for 8 weeks after the last dose. For males, surgical sterilisation should be applied or agreement to use an appropriate method of contraception for the duration of the trial or 8 weeks after the final dose.
 
(10) Subjects voluntarily enrolled in the study, signed an informed
 |

|                      |                                                                                                                                                                                                                                                                                                                                                                                                                                                                                                                                                                                                                                                                         |

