## 2 Background

Surgery is the primary modality for the treatment of resectable gastric cancer, and radiotherapy can improve local control rates, but does the benefit of local control with postoperative radiotherapy translate into a survival benefit? The landmark INT-0116 study demonstrated that postoperative adjuvant radiotherapy (45 Gy/25 doses) given after radical surgery for gastric cancer increased 3-year survival from 41% to 50% ( $P < 0.001$ ), and the NCCN guidelines recommend postoperative adjuvant radiotherapy for patients with postoperative stage T2N0M0 and above. However, the lack of standardisation of the surgical approach and the fact that D2 resection accounted for only 10% of the patients in this study have led to ongoing controversy. To address this issue, the Korean ARTIST phase III study focused on postoperative D2 patients and showed that concurrent radiotherapy (45 Gy/25 sessions) improved DFS by 5.2% in the lymph node-positive subgroup, although it did not improve overall DFS ( $P=0.0365$ ). This result suggests the need to re-evaluate the precise benefit of radiotherapy in the post-D2 population.

Moreover, our department has previously conducted a phase I/II clinical study of the FOLFOX regimen combined with synchronous radiotherapy (at a dose of 50.4 Gy) after gastric cancer surgery, which confirmed the efficacy and safety of 50.4 Gy of radiotherapy combined with synchronous chemotherapy. The results of the phase II clinical study showed that the 1- and 2-year OS and DFS of the FOLFOX regimen combined with synchronous after radical D2 surgery were 95%, 82% and 85%, 78%. And the phase I/II clinical study of SOX regimen combined with synchronous radiotherapy after gastric cancer has been completed, after which the maximum tolerated dose (maximum tolerated dose, MTD) and safety of S-1 during synchronous radiotherapy have been explored. On this basis, I expect to further develop this multicenter phase III randomized controlled clinical study to explore the value of SOX regimen combined with simultaneous radiotherapy in the adjuvant treatment of gastric cancer patients after D2 radical surgery.

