### **Contour Delineation Specifications for Postoperative Radiotherapy Target Volumes in Gastric Cancer**

The delineation of postoperative radiotherapy target volumes after D2 radical gastrectomy for gastric cancer primarily refers to the delineation of the CTV (Clinical Target Volume). Substantial differences may exist in target volume delineation across institutions and among clinicians. This may affect the quality of multicenter clinical studies. Therefore, this contouring specification is formulated to improve the consistency of radiotherapy planning in this clinical study.

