#### **II. CTV Delineation**

1. Postoperative radiotherapy target volumes for gastric cancer include the tumor bed, anastomosis, and regional lymph nodes. On each slice of the simulation CT images, the regions requiring radiotherapy should be delineated within a single CTV; that is, each region should not be contoured separately.

(1) Anastomosis:

- ① For distal one-third gastric cancer, the duodenal stump should be included in the CTV;
- ② For proximal one-third gastric cancer or tumors at the esophagogastric junction, the esophagojejunostomy should be included in the CTV;
- ③ For tumors at the esophagogastric junction, the CTV should extend cranially to include 4 cm of the esophagus (to cover paraesophageal lymph nodes).

(2) Tumor bed

- ① For gastric cancer with T stage T1-2, the CTV does not need to include the tumor bed;
- ② Anterior abdominal wall: only in gastric cancer with T stage T3-4, when preoperative imaging and/or the intraoperative surgeon's description indicates suspected or confirmed invasion of the anterior abdominal wall, or an indistinct interface between the tumor and the anterior abdominal wall, should the postoperative radiotherapy CTV include the anterior abdominal wall.

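### Inclusion criterion 5 is badly fixed: its nodal condition excludes nobody, and Appendix 2 has T-stage wording that cannot apply to the population it defines

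*Protocol*

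**What the plan says.** **Eligibility.** Criterion 5 in section 5.1 of the Protocol requires, under the 2010 UICC/AJCC staging, a postoperative pathological stage of "T stage $\geq$ T4a, N stage $\geq$ N0" and M0. The synopsis has the same wording. The T and N conditions are separated only by a comma. Criterion 3 says that "the number of lymph node dissection should be" at least 15.

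**Contouring.** Appendix 2 is not a borrowed general text. Its introduction says that "this contouring specification is formulated to improve the consistency of radiotherapy planning in this clinical study". Under II. CTV Delineation, item (2), it gives two rules that depend on T stage:

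- "For gastric cancer with T stage T1-2, the CTV does not need to include the tumor bed"
- The anterior abdominal wall is included "only in gastric cancer with T stage T3-4", and then only under stated conditions.

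**Other statements about the population.** The synopsis gives the target population as gastric carcinoma, with no stage. The Background mentions a guideline recommendation starting at T2N0M0. Neither sets eligibility. Section 10.3 assumes 3-year DFS of 70% in the control arm and 78% with radiotherapy, and gives no stage-specific source for the 70%.

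**The concern.** Criterion 5 decides which depth of invasion and which nodal status may enter the trial, and one of its two terms does no work. A threshold that nobody can fail prompts the question whether the threshold, or the word that should join it to the T condition, came out as intended. The trial's own contouring document adds to the doubt, because it provides for T stages that the criterion, read literally, never admits.

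The eligible stage range affects the event rate, the treatment effect that can be expected and the population to which the conclusion applies. It also determines whether 70% is a reasonable control rate. A multicentre trial needs a stage criterion that can be read in only one way.

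**Working it through.** No figure in the plan can be recomputed to settle this, so the check sets the texts side by side.

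**Step 1. What the nodal term does.** N0 is the lowest nodal category, so N at least N0 is true for every patient whose nodes were assessed. Criterion 3 asks for at least 15 dissected nodes, so nodal status should be known for every eligible patient. The term removes no one.

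**Step 2. What the comma can mean.**

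| Reading of criterion 5 | Who qualifies (M0, nodes assessed) | T term | N term | T1-2 rule in Appendix 2 | T3-4 rule in Appendix 2 |
|---|---|---|---|---|---|
| T *and* N | T4a and T4b, any N | restricts | idle | applies to nobody | applies to T4; T3 wording idle |
| T *or* N | every T, any N | idle | admits everyone | applies | applies in full |

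Under *and*, the natural reading of a list of conditions, the N term does nothing. Under *or*, the T threshold has no purpose. With the thresholds as printed, neither connective gives a criterion in which both terms restrict entry.

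**Step 3. Compare with Appendix 2.** Under the literal *and* reading, the T1-2 rule has no patient to act on. The other rule is a joint one. There is no separate T3 rule, and the joint rule still governs the T4a and T4b patients who can be enrolled. Only its mention of T3 fails to fit.

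**Step 4. Which explanations remain.**

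1. Criterion 5 is as intended, its N term simply means any N, and the T1-2 and T3 wording in Appendix 2 is redundant.
2. The T threshold is not the one intended.
3. The N threshold or the connective is not the one intended.

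The Protocol has no statement that chooses among these. Section 4.4 lists the tumour bed as part of the target volume with no exception by T stage, but it refers to the contouring annex for detail, so it does not decide the matter either.

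**Step 5. Link to section 10.3.** The control rate of 70% is the planning figure that most directly depends on the stage range. Because no stage-specific source is given, a reader cannot tell whether it was chosen for T4a or deeper with any N, or for some other range.

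**The case against.** The strongest reply is that nothing here defines two populations. Eligibility is set by criterion 5 alone, and its two copies agree. Appendix 2 states no eligibility. Its rules are conditional on T stage, and a rule conditional on T1-2 is merely idle if no such patient is enrolled. A site that screens a T2 or T3 patient finds that criterion 5, read literally, excludes them. The nodal term also has an ordinary explanation: the Background writes a guideline's stage floor as T2N0M0, and criterion 5 may be the same kind of notation for T4aN0M0 upwards. All of this stands, so a reader should not infer that the protocol contradicts itself on who is studied, or that one of the passages must be wrong.

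Two further inferences are tempting and are not supported.

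- **That the trial's rationale is benefit in node-positive patients, which criterion 5 then fails to require.** The Background does report that a Korean phase III trial in D2 patients "improved DFS by 5.2% in the lymph node-positive subgroup" without an overall gain. But it also cites a survival benefit from an earlier postoperative radiotherapy trial, the guideline, and the department's own phase I/II work. It concludes that the benefit needs re-evaluation in the post-D2 population as a whole.
- **That enrolling N0 patients would dilute the effect by a calculable amount of power.** The documents give no N0 share, no estimate of effect in N0 patients and no control rate by nodal status. Any power figure would rest wholly on assumptions.

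What the reply does not remove is that half of the stage criterion is uninformative, and that a document written for this trial has wording that does not fit the population the criterion defines.

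**Conclusion.** The point holds as a defect of specification. As printed, criterion 5 reduces to T4a or deeper with any N, provided that the comma means *and* and that nodes were assessed as criterion 3 implies. Appendix 2 has one rule (T1-2) and part of another (the T3 in T3-4) that cannot apply to that population. Whether criterion 5 is miswritten or Appendix 2 is redundant cannot be decided from the documents, and this review takes no position on which stage range is right.

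The consequence is qualitative: uncertainty about the intended population, and hence about what the 70% control rate and the trial's conclusion refer to. It should be corrected because it concerns the rule that decides who is randomised, and because correcting it costs little.

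**What to change.** 1. The investigators should state the intended stage range as an explicit list of eligible pT/pN categories, worded identically in the synopsis and section 5.1. The N term should either restrict entry or be deleted, and any *and* or *or* should be written out.
2. Reconcile the T-stage wording in Appendix 2, II. CTV Delineation (2), with that list. The joint T3-4 rule must not be struck as a whole, because it governs T4 patients who are eligible under the present text.
3. Confirm in section 10.3 that the 70% control 3-year DFS refers to the listed population, or revise it.
4. Optional: prespecify pN0 versus pN+ as a factor in the Cox analysis of DFS. Pathological N stage is already needed for criterion 5. A statistical analysis plan may already cover this, and the point does not depend on it.

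Items 1 and 2 change wording only. Item 3 is a sentence of confirmation, unless the 70% turns out to describe a different population; the sample size would then have to be revisited. Item 4 adds one term to a model. None requires extra procedures.
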